**Table 1. Illustrative examples of intervention construction**

|                                                                   |                                                                                |                                                                                                                                       |                                                                                                                                                                                       |
|-------------------------------------------------------------------|--------------------------------------------------------------------------------|---------------------------------------------------------------------------------------------------------------------------------------|---------------------------------------------------------------------------------------------------------------------------------------------------------------------------------------|
| Clinical behaviour targeted                                | Performing an immediate lumbar puncture in a patient without contraindications | Investigating CSF for cell count, protein and CSF to plasma glucose ratio                                                             | Starting treatment with aciclovir within 6 hours in patients with suspected encephalitis                                                                                              |
| Determinant of behaviour targeted (domain from interviews) | Lack of knowledge of relevant clinical history and signs (knowledge)           | Inability to recall all required investigations (memory, attention and decision processes)                                            | Erroneous beliefs about consequences of not starting treatment (beliefs about consequences); not perceived as standard practice (social influences)                                   |
| Behaviour change technique(s)                              | Awareness raising                                                              | Provision of prompts, triggers and cues                                                                                               | Persuasive communication; social pressure and modelling                                                                                                                               |
| Intervention delivery method(s)                            | Educational meetings; printed educational materials                            | (Easily available) departmental protocols and computerised pathways; prompts in electronic or paper forms for ordering investigations | Educational meetings outlining evidence base and incorporating patient narratives to illustrate consequences of delayed treatment; demonstration of appropriate use by opinion leader |

## 7 ASSESSMENTS AND PROCEDURES

### 7.1 Data collection

Data will be collected by a trained member of hospital staff (eg research nurses, the principal investigator, the co-investigator or a member of their team). The data will be pseudo- anonymised during the completion of the case report form (CRF) with the study number acting as the encryption key (please see below for details). Data will be collected for the previous 12 months and then again in 12 months' time.

### 7.2 Other Assessments

#### Cost-effectiveness analysis

*Methods.* Quantities of resource utilisation will be collected from trial records, while unit costs will be obtained from publicly available data published routinely. Costs related to inputs associated with health care services as used in the trial will be

estimated at its conclusion. Costs and health benefits occurring after 12 months will be discounted at 3.5% per annum. Therefore, results will include, in addition to incremental costs and benefits, an estimate of total cost per patient for each arm. In order to estimate Quality Adjusted Life Years (QALYs), utility values will be estimated from the results of administering the SF-36 and EQ-5D in the Quality of Life sub-study, following Brazier's methodology (14). Estimates of costs and health outcome (utilities) will be used to populate a model of encephalitis patient management under the status quo and the alternative under new guidelines being adopted. The model will cover the remaining patient lifetime within which the (probability of) cost-effectiveness of the alternative will be analysed (15).

*Statistical Methods.* Cost data will be analysed using regression methods for handling censored cost data. Costs and benefits will be analysed jointly using a bivariate probability distribution. Sample uncertainty in estimated cost difference and Incremental Cost-Effectiveness Ratios (ICERs) between arms groups will be described using bootstrapped confidence intervals (16). Data analysis will be performed using a suitable statistical package such as R or STATA.

*Uncertainty Analysis of Decision Model Results.* Parameter uncertainty will be accounted for through univariate sensitivity analysis and probabilistic sensitivity analysis.

## **7.3 Trial Closure**

The site shall be deemed as closed after the data at 12 months has been completed and all data queries resolved. When this has happened at all sites the database will be locked.

# **8 STATISTICAL CONSIDERATIONS**

## **8.1 Randomisation**

To ensure the best quality data within this study control and intervention sites must not have any routine crossover of staff between them, for example, trainee doctors moving as part of the standard rotation pattern within their training deanery. Therefore, we will take deanery boundaries into account during recruitment and

randomise using the deaneries as randomisation units. We intend to include a range of types of hospital in the trial to improve generalisability. The mix of these should broadly represent national provision. We will use deanery as the unit of randomisation, to guard against leakage of information between hospitals within the same deanery as trainee doctors move between hospitals. We will define two blocks of deaneries, a block of 6 in which research teams are currently actively involved in the ENCEPH UK programme and a block of 6 in which research teams are not currently actively involved in the ENCEPH UK programme. An independent statistician will randomise equal numbers within each block to the intervention and routine arms.

## 8.2 Outcome Measures

The primary endpoint will be aciclovir administration within 6 hours and an LP performed within 12 hours of admission to hospital for patients with a suspected CNS infection.

The outcome measures will assess all primary and secondary outcomes as detailed above and a time to event analysis will be performed for each of these. We will also conduct an analysis of outcome measures between adults and paediatric populations.

## 8.3 Sample Size and Analysis

Using pilot data from 315 patients across 26 hospitals in 4 deaneries we have estimated the standard deviations of the deanery and hospital random effects to be 0.244 and 1.108, respectively, and the current proportion of compliance under treatment as usual as 0.05. Using these estimates, the table below shows the power of the likelihood ratio test for a significant difference between standard care and the intervention as a function of  $m$ , the number of patients recruited per hospital, and  $p$ , the compliance proportion under the intervention (Table 2).

Table 2.

|    | P     |       |       |
|----|-------|-------|-------|
| m  | 0.15  | 0.20  | 0.25  |
| 10 | 0.487 | 0.707 | 0.845 |
| 15 | 0.547 | 0.777 | 0.907 |
| 20 | 0.590 | 0.809 | 0.921 |
| 25 | 0.606 | 0.832 | 0.937 |

On the basis of these results, recruiting 20 patients per hospital should achieve a power of at least 0.8 when the compliance proportion under the intervention is 0.20. To allow for possible under-recruitment in some of the smaller hospitals, we will therefore seek to recruit up to 30 patients per hospital, per notes review (two reviews within this study) with a mix of adult and paediatric cases to be included. This will result in 840 cases in each of the two reviews, giving a total of 1680.

We will analyse the results in STATA or R using a generalised linear mixed model (17) with binomial errors, logistic link, fixed effects for blocks and treatments, random effects for deanery and for hospital.

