# 1 PROTOCOL SUMMARY

**Title:** Development and evaluation of an intervention based around the National guidelines on the management of suspected encephalitis, and its evaluation through a cost effectiveness analysis.

**Population:** Secondary care hospitals in the UK will be included. Hospital sites already participating in the ENCEPH-UK study will be excluded so as to reduce the risk of attention bias.

**Number of Sites:** Up to twenty eight secondary care hospitals will be recruited across the UK.

**Study Duration:** Fifteen months per site (to include delivery and evaluation of an intervention at 12 months).

**Description of Intervention:** The intervention will target clinicians (and other healthcare workers) within the hospitals.  
Outcome data will be collected on patients (adults and children) with suspected or confirmed encephalitis.

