### **10.3 Data Capture Methods**

#### **Data collection**

As we have done previously, a combination of methods to identify patients with suspected encephalitis involving screening of electronic sources (2, 3):

- Hospital discharge codes;
- Laboratory records for patients who have had a CSF sample taken;
- Pharmacy records for patients who have received intravenous aciclovir;
- Radiology records where 'suspected encephalitis' or other potential marker terms are used.

The first two methods will be applied across all sites to minimize identification biases associated with any one method.

Trained members of NHS staff (eg nurses, the principal investigator, the co-investigator or a member of their team) will undertake retrospective case identification and data collection at each hospital site. The records of suspected and confirmed cases will be reviewed and data collected using a standardised form to document processes and selected outcomes of care. Data will be collected for the 12 months prior to and 12 months after the intervention period. It is unlikely that

masked allocation to intervention or control hospital sites will be feasible during data collection but the feasibility of this will be reviewed.

The date and time from initial presentation to hospital, either via accident and emergency or medical admissions, will be taken as the starting point for data extraction and outcome measurement. As patients may be transferred between centres, patients within both groups will be characterised and the data analysed as per an intention to treat analysis.

Clinical data collection will be based upon the audit tool developed for the National Guideline. Apart from basic demographic data (for example date of birth and sex), no patient identifiers will be used, so that only sufficiently anonymised case records are transferred out of hospital settings for analysis. No one outside of the direct healthcare team will have access to any patient identifiable data as this will be pseudo-anonymised at site.

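### Section 8.3 fixes a primary model without a period or baseline term and does not say which notes review enters it or how pre-intervention charts are coded

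*Protocol*

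**What the plan says.** Section 10.3 of the protocol, under Data collection, plans two chart collections at every site: "Data will be collected for the 12 months prior to and 12 months after the intervention period". Section 8.3 gives the volume: "This will result in 840 cases in each of the two reviews, giving a total of 1680".

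The sample size in section 8.3 uses pilot estimates: "standard deviations of the deanery and hospital random effects to be 0.244 and 1.108, respectively, and the current proportion of compliance under treatment as usual" of 0.05. From Table 2 it concludes that "recruiting 20 patients per hospital should achieve a power of at least 0.8 when the compliance proportion under the intervention is 0.20".

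The analysis paragraph comes directly after the total for the two reviews. It names a binomial mixed model with logistic link and "fixed effects for blocks and treatments, random effects for deanery and for hospital". It has no term for review period, no baseline covariate and no treatment-by-period term. It does not say whether one review or both are analysed, or what value the treatment variable takes for a chart from the year before the intervention.

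The end of section 4 mentions a time series analysis of all outcomes, but gives no model and does not tie it to the primary test in section 8.3.

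**The concern.** The protocol lists the terms of its primary model, so an SAP that follows the list inherits the gap and one that adds terms departs from the protocol. The same sentence supports three analyses:

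- **Second review only.** A valid randomised comparison, but the baseline charts play no part in the estimate. At the rates in section 12 the first review costs up to 28 × £150 + 840 × £15 = £4,200 + £12,600 = £16,800.
- **Both reviews, treatment coded as the arm.** Pre-intervention charts, which cannot show an effect, are averaged with post-intervention charts.
- **Both reviews, treatment switched on only after the intervention, no period term.** There is no dilution, but any change over time common to both arms is partly credited to the intervention.

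Section 10.3 says that masking during data collection is unlikely to be feasible. The choice among these analyses should therefore be written down before outcomes are seen.

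**Working it through.** **Inputs from the protocol.** Control compliance 0.05, target 0.20, deanery SD 0.244, hospital SD 1.108, m = 20 patients per hospital (section 8.3); "power of the likelihood ratio test for a significant difference between standard care and the intervention" (section 8.3); "Up to twenty eight secondary care hospitals will be recruited across the UK" (section 1); 12 deaneries in two blocks of 6, where "An independent statistician will randomise equal numbers within each block to the intervention and routine arms" (section 8.1).

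**Assumptions.** Two-sided 5% level (not stated in section 8.3), so the likelihood ratio statistic is compared with 3.84. SDs are on the logit scale and proportions are conditional on random effects of zero. There are 14 hospitals per arm, two or three per deanery.

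**Basic quantities.** The true log odds ratio is logit(0.20) − logit(0.05) = −1.386 + 2.944 = 1.558. The between-cluster variance is 0.244² + 1.108² = 0.060 + 1.228 = 1.287, of which 1.228/1.287 = 95% is at hospital level.

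**Step 1: reproduce Table 2.** Power was simulated by fitting the section 8.3 model by Gauss-Hermite quadrature to one review, 28 hospitals in 12 deaneries. There were 1,000 replicates for m = 20, p = 0.20 and 500 for the other cells. The m = 15 row was not run.

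| m | p | Table 2 | One review, simulated |
|---|---|---|---|
| 10 | 0.15 | 0.487 | 0.500 |
| 10 | 0.20 | 0.707 | 0.728 |
| 10 | 0.25 | 0.845 | 0.862 |
| 20 | 0.15 | 0.590 | 0.612 |
| 20 | 0.20 | 0.809 | 0.809 |
| 20 | 0.25 | 0.921 | 0.936 |
| 25 | 0.15 | 0.606 | 0.640 |
| 25 | 0.20 | 0.832 | 0.832 |
| 25 | 0.25 | 0.937 | 0.938 |

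Every difference is within about two Monte Carlo standard errors. For example, the key cell has SE √(0.809 × 0.191/1000) = 0.012. Table 2 is therefore consistent with a comparison of one review.

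**Step 2: both reviews with only the listed terms** (m = 20 per review, 0.05 against 0.20, 400 replicates, no secular trend).

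- Arm indicator: median log odds ratio 0.95, against 1.57 from the second review alone; power 0.50.
- Indicator on only after the intervention: median log odds ratio 1.56, power 1.00, so no dilution.

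Next, suppose there is no intervention effect and compliance rises from 5% to 10% in both arms, a logit shift of −2.197 + 2.944 = 0.747. This trend is illustrative. Rejection rates in 300 replicates were 66% for the switched-on indicator without a period term, 8% for the same indicator with one, and 7% for the second review alone. The Monte Carlo SE of the last two is about 1.5 points.

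**Step 3: what the first review could add** (m = 20 per review). The protocol gives no between-review correlation of hospital effects, so it is varied.

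| Analysis | corr. 1.0 | corr. 0.8 | corr. 0.5 |
|---|---|---|---|
| Second review, baseline log-odds covariate | 0.93 | 0.88 | 0.82 |
| Same covariate, continuity-corrected, simpler simulation (hospital effect only, 200 replicates) | 0.98 | 0.90 | 0.87 |
| Both reviews, period term, arms equal at baseline | 0.985 | 0.96 | not run |
| Both reviews, period, arm and arm-by-period | 0.96 | 0.91 | not run |

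The second review alone gave 0.77 in the code used for the first row, 0.80–0.86 in that for the second, and 0.81 in that for the last two. At correlation 0.5 the gain is thus about 5 points in the first row (0.82 against 0.77) and 1 to 7 points in the second. The joint fits at 0.8 left out a hospital-by-period effect, so they are somewhat optimistic.

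**Step 4: can baseline log-odds be computed?** The expected share of hospitals with no compliant chart among n is E[(1 − p)ⁿ], with logit p normal with mean −2.944 and SD √1.287 = 1.135. This gives 38% for n = 20 and 28% for n = 30. If 0.05 is a marginal proportion, the shares are 51% and 41%. Raw log-odds would be undefined in those hospitals.

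**The case against.** The strongest reply is that section 8.3 is coherent as it stands. Table 2 reproduces from one review, so the natural reading is a second-review comparison with block adjustment and deanery and hospital random effects. That comparison is randomised and has the stated power, and its standard error already allows for chance imbalance between hospitals. The choice of data set and covariates is often left to an SAP, which is not at hand, and section 4 does announce a time series analysis. The gain from baseline adjustment also depends on a correlation that no section supplies.

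Most of this stands. A reader might infer that the protocol sets the first review aside, that the primary analysis has only half the planned power, or that the only choice is between dilution and discarding data. The documents support none of these. Section 8.3 never says that the first review is unused. Power near 0.5 arises only if pre-intervention charts in the intervention arm are coded as treated, which nothing in the text requires. The switched-on coding uses all charts without dilution, though at the price of confounding with time.

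The appeal to the SAP does not fully answer the point. The protocol itself lists the terms, and with those terms only the unstated second-review reading is safe.

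**Conclusion.** The point holds as a lack of specification with an efficiency cost, not as an error that invalidates the primary analysis. On the reading best supported by Table 2, the analysis is valid with power of about 0.81 at m = 20. What it gives up is baseline adjustment, which would bring power to about 0.82–0.98 for correlations of 0.5–1.0, with little gain at the low end. With both reviews and only the listed terms, power is about 0.5 under one coding. Under the other, false rejection is 66% in the illustrative 5% to 10% trend.

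These figures rest on a two-sided 5% level, 28 hospitals, logit-scale SDs and assumed between-review correlations. They are at m = 20, whereas section 8.3 seeks up to 30. The null rejection rates of 7% and 8% are slightly above nominal, so the powers are not compared at exactly equal size. Severity: a cheap improvement plus protection against a misread model.

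**What to change.** In section 8.3, name the review(s) in the primary model and the treatment coding, and choose one of two analyses:

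1. Estimate the treatment effect on second-review charts, adjusted for the hospital's first-review compliance. Enter this as log-odds with a stated correction, for example log[(y + 0.5)/(n − y + 0.5)] for y compliant charts of n, because many hospitals will have y = 0.
2. Fit both reviews jointly with fixed effects for block and period, treatment active only in the second review (arms equal at baseline), and random effects for deanery, hospital and hospital-by-period.

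Either way, state that no first-review chart is coded as treated. The change needs wording in section 8.3 and matching text in the SAP, and no new data. The first option costs one covariate degree of freedom. The second costs one extra variance component, which may be poorly estimated with so few baseline events per hospital.

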## **9 ETHICAL CONSIDERATIONS**

### **9.1 Ethical Considerations**

This study is encouraging 'best' healthcare in both the intervention and the control arms. The study will abide by the principles of the Research Governance Framework and ICH GCP. The study intervention will target clinicians and pseudo-anonymised patient data will be used to assess changes in clinical practice. Patients' records will be viewed by a member of NHS staff working at that site with medical information extracted using a CRF which will record a unique study number and patient date of birth but no other identifiers will be recorded.

### **9.2 Ethical Approval**

The trial protocol has received the favourable opinion from Preston North West Multi-centre Research Ethics Committee (MREC) and will undergo site specific assessment (SSA) by completing section C of the REC application form.

### **9.3 Regulatory Approval**

R&D approvals will be sought from each research sites before commencement of the study. Furthermore, an International Standard Randomised Controlled Trial Number (ISRCTN) number will be in place before the first site is actively opened.

## **10 TRIAL MONITORING**

This study will be monitored via a central risk based approach as per the agreed monitoring plan.

### **10.1 Risk Assessment**

An appropriate risk assessment will be completed and its resulting procedures followed during the study. As this study does not directly involve patients, or affect their care, this study will have low to zero risk attached to it.

### **10.2 Source Documents**

Source data is all information, original records of clinical findings, observations, or other activities in a clinical trial necessary for the reconstruction and evaluation of the trial. Each participating site will maintain appropriate medical and research records for this trial, in compliance with ICH E6 GCP, Section 4.9 and regulatory and institutional requirements for the protection of confidentiality of subjects.

### **10.3 Data Capture Methods**

#### **Data collection**

As we have done previously, a combination of methods to identify patients with suspected encephalitis involving screening of electronic sources (2, 3):

- Hospital discharge codes;
- Laboratory records for patients who have had a CSF sample taken;
- Pharmacy records for patients who have received intravenous aciclovir;
- Radiology records where 'suspected encephalitis' or other potential marker terms are used.

The first two methods will be applied across all sites to minimize identification biases associated with any one method.

Trained members of NHS staff (eg nurses, the principal investigator, the co-investigator or a member of their team) will undertake retrospective case identification and data collection at each hospital site. The records of suspected and confirmed cases will be reviewed and data collected using a standardised form to document processes and selected outcomes of care. Data will be collected for the 12 months prior to and 12 months after the intervention period. It is unlikely that

masked allocation to intervention or control hospital sites will be feasible during data collection but the feasibility of this will be reviewed.

The date and time from initial presentation to hospital, either via accident and emergency or medical admissions, will be taken as the starting point for data extraction and outcome measurement. As patients may be transferred between centres, patients within both groups will be characterised and the data analysed as per an intention to treat analysis.

Clinical data collection will be based upon the audit tool developed for the National Guideline. Apart from basic demographic data (for example date of birth and sex), no patient identifiers will be used, so that only sufficiently anonymised case records are transferred out of hospital settings for analysis. No one outside of the direct healthcare team will have access to any patient identifiable data as this will be pseudo-anonymised at site.

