**The secondary outcomes will be:**

- The proportion of all adults given intra venous (IV) aciclovir for a neurological presentation who met the definition of suspected encephalitis.
- The proportion of all children given IV aciclovir for a neurological presentation who met the definition of suspected encephalitis.
- The proportion of patients with suspected encephalitis who had a lumbar puncture performed within 12 hours unless there was a clinical contraindication.
- The proportion of patients with suspected encephalitis who had a lumbar puncture after resolution of a clinical contraindication to that LP.
- The proportion of patients with suspected encephalitis who had either Magnetic Resonance Imaging (MRI) or Computer Tomography (CT) scan within 24 hours of admission.
- For patients with HSV encephalitis, the proportion who die, have sequelae and appear to make a full recovery upon discharge.
- The proportion of patients with suspected encephalitis having had a lumbar puncture, who had the following CSF investigations performed:
  - CSF:serum glucose ratio calculated
  - HSV PCR performed
- An evaluation of the primary outcomes comparing adults and children enrolled in the RCT.
- A cost effectiveness evaluation of the intervention.

\* Suspected encephalitis is defined as febrile illness or history of a febrile illness with altered behaviours, cognition, personality, or consciousness or new seizures or new focal neurological signs (please see section 5.1 for details).

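### Section 10.3 leaves pharmacy and radiology searches optional, so the two IV aciclovir outcomes have no assured denominator and entry to the primary denominator depends partly on having had an LP

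*Protocol*

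**What the plan says.** Protocol section 10.3 (Data collection) names four electronic sources:

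1. "Hospital discharge codes"
2. "Laboratory records for patients who have had a CSF sample taken"
3. "Pharmacy records for patients who have received intravenous aciclovir"
4. "Radiology records where 'suspected encephalitis' or other potential marker terms are used"

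It then states: "The first two methods will be applied across all sites to minimize identification biases associated with any one method". Nothing says at which sites, or by what rule, sources 3 and 4 are used. Trained NHS staff "will undertake retrospective case identification and data collection at each hospital site", and the protocol calls it unlikely that "masked allocation to intervention or control hospital sites will be feasible during data collection but the feasibility of this will be reviewed".

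These places depend on that search:

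- **Primary outcome (sections 1 and 4).** Aciclovir within 6 hours, and an LP within 12 hours unless contraindicated, among patients with suspected encephalitis.
- **First two secondary outcomes.** For adults: "The proportion of all adults given intra venous (IV) aciclovir for a neurological presentation who met the definition of suspected encephalitis". The second is the same for children.
- **LP secondary outcome.** LP within 12 hours, with the same exemption.
- **Eligibility (section 5.1, b and c).** Patients under clinical suspicion whose investigations are incomplete are eligible, so suspected cases without an LP belong in the denominator.
- **Section 6.** Failure to perform a diagnostic LP when there is no contraindication is one of the deviations singled out for attention.

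**The concern.** The sentence in section 10.3 gives reduction of identification bias as its reason, but the pair of sources it fixes does not achieve that.

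- **Aciclovir outcomes.** They need a list of everyone given IV aciclovir for a neurological presentation. Where pharmacy records are not searched, treated patients are seen only if they also had a CSF sample or a relevant discharge code (or a radiology marker, if that source is used). Those patients plausibly meet the case definition more often, so the level may be too high. Sites with and without the pharmacy search are not comparable.
- **Primary and LP outcomes.** One of the two universal sources admits a patient only because an LP was done. If LP use changes with allocation, so does the set of patients found. This selection arises after randomisation, and the baseline review cannot remove it because the shift follows the intervention. The choice of extra sources is also left to sites that probably know their allocation.

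Patients who were never identified cannot be recovered at analysis, so the protocol has to settle this before data collection.

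**Working it through.** The plan gives no figure for case capture, so there is none to reproduce. Section 8.3 supplies compliance of 0.05 under usual care and 0.20 under the intervention, a true odds ratio of (0.20/0.80)/(0.05/0.95) = 4.75. The power calculation there is not in dispute: simulation of its model gave 0.796 against the stated 0.809 (20 patients per hospital, two-sided 0.05 assumed). Everything below is illustration under assumed rates.

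**Primary outcome.** Let L be the share of suspected cases with an LP and c the true compliance. Assume that the CSF log finds every LP patient, that other sources find a share s of patients without an LP, and that every compliant patient had an LP. Then

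observed compliance = c / D, with D = L + s(1 − L).

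- *Wide range: L of 40–70% under usual care, 80–90% under intervention, s of 0.2–0.8.*
  - Strongest distortion (40%, 90%, s = 0.2): D is 0.52 and 0.92. With compliance unchanged at 0.05 the observed rates are 0.096 and 0.054, OR 0.54. With 0.05 and 0.20 the OR is 4 × (0.52 − 0.05)/(0.92 − 0.20) = 2.6.
  - Weakest distortion (70%, 80%, s = 0.8): D is 0.94 and 0.96. The ORs are 0.98 and 4 × 0.89/0.76 = 4.7.
- *Moderate case: L of 60% and 80%, true 0.05 and 0.20.*

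| s | Observed usual care | Observed intervention | OR | Difference |
|---|---|---|---|---|
| 0.25 | 0.071 | 0.235 | 4.0 | 0.164 |
| 0.50 | 0.062 | 0.222 | 4.3 | 0.160 |
| 0.75 | 0.056 | 0.211 | 4.5 | 0.155 |
| True | 0.05 | 0.20 | 4.75 | 0.15 |

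Both rates are inflated. The OR, which is the scale of the planned logistic model, is attenuated, while the simple difference is slightly enlarged.

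- *Direction.* From the formula, the OR is attenuated only if (1 − L0)/(1 − c0) exceeds (1 − L1)/(1 − c1), where 0 is usual care and 1 is intervention. With 0.05 and 0.20 this means 1 − L0 > 1.1875 × (1 − L1), since 0.95/0.80 = 1.1875. All the cases above satisfy it. If compliance rose through faster rather than more LPs, it could fail: with L = 50% in both arms and s = 0.5, D = 0.75, the observed rates are 0.067 and 0.267, and the OR is 4 × 0.70/0.55 = 5.1.

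**LP ever done**, true 60% and 80%, observed L/D:

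- s = 0.25: 85.7% and 94.1%, difference 8.4 points
- s = 0.50: 75.0% and 88.9%, difference 13.9 points
- s = 0.75: 66.7% and 84.2%, difference 17.5 points

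The true difference is 20 points. The OR stays at (0.8/0.2)/(0.6/0.4) = 2.67, because a common s cancels. The distortion here is in the proportions and their difference.

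**Aciclovir outcome.** Assume half of those treated meet the definition, LP is done in 80% of these and 30% of the others, and codes find 40% and 5% of those without an LP. Per 100 treated, 50 × (0.8 + 0.2 × 0.4) = 44 and 50 × (0.3 + 0.7 × 0.05) = 16.75 are found. Observed 44/60.75 = 0.72 against a true 0.50. Alternatively, with 90% of those meeting the definition found and 30%, 50% or 70% of the others, the observed value is 0.75, 0.64 or 0.56. There is no distortion if capture does not depend on meeting the definition.

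**The case against.** Several points for the plan stand.

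- **The selection is partial.** Discharge codes find patients without an LP, and pharmacy or radiology searches find more wherever they are used. The two universal sources are a minimum.
- **The CSF log is not the outcome.** It records any LP at any time. With usual-care compliance at 0.05, many patients on it may fail the primary outcome.
- **The arithmetic simplifies.** A patient with a contraindicated LP can meet the primary outcome without one, and the formula ignores such patients. The LP and capture rates are assumed, and the OR of 0.54 comes from the extreme corner of the range.
- **No between-arm bias is shown for the aciclovir outcomes.** The illustration concerns their level.

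A reader might infer that a suspected case without an LP is a certain failure that is never found. The contraindication exemption and the optional sources rule that out. A reader might also infer that the trial could show a benefit where none exists. In the illustrations, with compliance unchanged and LP use higher under the intervention, the OR falls below 1; with equal LP use and equal capture it is 1.

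None of this supplies the missing rule for pharmacy and radiology searches, or a denominator for the aciclovir outcomes where pharmacy records are not searched.

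**Conclusion.** The point holds in a limited form.

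The firm part needs no assumed rate: the protocol defines two secondary outcomes on all patients given IV aciclovir and does not require, at every site, the only listed source that selects on that treatment. Their denominator is not assured, and sites may not be comparable. It does not follow that the denominator is missing everywhere.

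The second part is conditional. At sites using only the universal sources, entry to the primary and LP denominators depends partly on LP. If the intervention raises LP use as in the ranges shown, the primary OR is attenuated (4.75 appears as about 2.6 to 4.7, or 4.0 to 4.5 in the moderate case) and absolute rates are inflated. The documents contain no LP or capture rates, so neither the size nor, in every case, the direction can be fixed from them. They do not support a claim that the primary comparison is invalid. They support a cheap correction that must be made before cases are identified.

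**What to change.** Amend section 10.3 as follows:

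- Apply all four listed sources identically at every site and in both reviews. At a minimum, add pharmacy to the first two, and use radiology either everywhere or nowhere.
- Use pharmacy IV aciclovir records as the sampling frame for the two aciclovir outcomes, screened for a neurological presentation.
- For the primary outcome, use the union of all mandated sources. Discharge codes plus pharmacy alone would select on aciclovir, the other half of that outcome.
- Record every source that identified each case. Run sensitivity analyses that exclude, in turn, cases found only through the CSF log and cases found only through pharmacy. Each exclusion mostly removes failures (no aciclovir, or no LP), so the results show dependence on the source and are not corrected estimates.

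The cost is protocol wording plus extra listing and screening from sources the protocol already names. It will be harder where dispensing is not electronic.
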